#### Data acquisition from routine care

2.3.3.

Information from routine care is retrieved repeatedly throughout the observation period from treating neurologists. The baseline data set comprises information on diagnosis and comorbidities, most recent relapse including its treatment and clinical outcome and full list of current medication as well as EDSS and MSFC-3, if performed routinely. Follow-up data are requested from any clinical visit throughout the observation period, at least semiannually, and comprise clinician’s global ratings of change, information on relapses since last visit in medication or comorbidities, as well as EDSS and MSFC-3.

#### Data acquisition at annual study visits

2.3.4.

##### Study assessment

2.3.4.1.

Time since diagnosis of multiple sclerosis, prior manifestations of disease, current symptoms, prior and current disease modifying therapy, supportive therapy and relapses in past 24 months as well as comorbidities and changes thereof are acquired by the clinical investigator.

Current therapy will be documented at baseline and changes thereof will be reported at each visit. This also extends to rehabilitative interventions.

##### Expanded disability status scale

2.3.4.2.

The expanded disability status scale (EDSS) is used to quantify disability in MS. The scale was first developed by Kurtzke in 1955 and then expanded in 1983. It is usually referred to as a measure which is scaled on 10 steps from 0 (no disability) to 10 (death from MS). Scoring is based on an examination by a neurologist. EDSS steps 1.0 to 3.5 refer to people with MS who are able to walk without any limitation, while EDSS steps 4.0 and higher are defined by decrease in walking capacity. Assessment of EDSS will follow instructions of Neurostatus for functional systems scores and EDSS step (59) by certified raters. In our study, the 3 m-CDP is defined as a 1.0 step increase from baseline EDSS when baseline EDSS was 0.0 to 5.0 and 0.5 step increase from baseline when baseline EDSS was 5.5 to 6.5, rated at 24 months with change confirmed at month 27.

##### Multiple sclerosis functional composite (MSFC-3 and MSFC-4)

2.3.4.3.

The MSFC was developed by a special Task Force on Clinical Outcomes Assessment as a clinically applicable standardized, quantitative assessment instrument for use in MS trials (35). The MSFC-3 measures three clinical dimensions: leg function/ambulation using the Timed 25-foot Walk test; arm/hand function using the 9 Hole Peg Test (9HPT); and cognitive function using the Paced Auditory Serial Addition Test (PASAT-3 version). Because the PASAT is not popular among patients and given the relevance of visual dysfunction in MS, an expert group (60), convened by the National MS Society, recommended two adaptations to the MSFC: (1) inclusion of the Sloan Low Contrast Letter Acuity test (60) (MSFC-4) and (2) use of the oral version of the Symbol Digit Modalities Test (SDMT) instead of the PASAT-3. In our study, the MSFC-4, will be administered on occasion of the annual visit at study site by a trained rater. In addition, the MSFC-3 will be collected from routine clinical visits semiannually. Both versions will use SDMT for the cognitive component.

The MSFC will be performed and analyzed in accordance with the respective testing manual issued by.

the National Multiple Sclerosis Society. Cut-offs for clinically meaningful change in MSFC and component Z-scores have been defined as >20% worsening (61).^1^

##### The 6-min walk

2.3.4.4.

The 6-min walk (6 MW) is applied here to measure of walking endurance/ walking capacity in pwMS (62). The test is characterized by good practicability, reproducibility and reliability in MS. Furthermore, ecological validity is supported by strong correlation to patient report of ambulation and physical fatigue (63). A ≥ 20 m decrease in distance covered in the 6-min walking test at comfortable speed is usually considered clinically meaningful (64).

##### Supervised operator-based assessment of motor function (Motognosis Labs PASS-MS)

2.3.4.5.

Our group developed a clinically applicable assessment protocol (PASS-MS) for usage with the Motognosis Labs system (Motognosis GmbH, Berlin, Germany). Motognosis Labs functions similar to Amsa in terms of technology. It differs *in camera* version used (Microsoft Kinect v2 for Motognosis Labs vs. Azure Kinect for Motognosis Amsa) and test set-up, as Motognosis Labs uses a camera plugged in to a laptop and participants are guided through assessments by a trained operator according to standard instructions.

PASS-MS consists of 10 short motor tasks performed in front of the RGB-D camera and parameters for the description of performance are generated by custom scripts. In operator-based application, this system proved acceptable to patients and was easily applied. Previous validation showed accuracy of derived parameters against gold standard multi-camera motion capture (33) and sufficient reliability and validity to measure balance and gait function in MS (65, 66).

Assessment of PASS-MS includes:Stance with open and closed eyes and closed feet (20s eyes open, 20s eyes closed).Dual Task Stance with open and closed eyes and closed feet.Stepping on place (40s).Short walk in comfortable speed.Short walk in maximum speed.Line walk.Standing up and sitting down from a chair.Pronator drift test.Finger-to-nose-test.Finger tapping.

##### Magnetic resonance imaging

2.3.4.6.

In this study a standardized MR protocol was performed consisting of: a 3D-T1-weighted sequence (MPRAGE), a 3D T2-SPACE, a 3D fluid attenuated inversion recovery (FLAIR), a Diffusion Weighted Imaging sequence (DWI) and a resting state functional MRI (rsfMRI). To define progression, we use operational cut-offs for brain volume loss known to increase with age. Mean BVL per year amounts to by 0.15, 0.30, 0.46, and 0.61% of baseline brain volume at ages 45, 55, 65, and 75 years, respectively (67). The corresponding age-dependent 95th percentiles of BVL per year were 0.52%, 0.77%, 1.05%, and 1.45%. Pathological BVL can be assumed if an individual BVL per year exceeds these thresholds for a given age (67).

##### Optical coherence tomography

2.3.4.7.

Optical coherence tomography (OCT) is a suitable high-resolution imaging method for the assessment of retinal integrity with good reproducibility. Peripapillary retinal nerve fiber layer thickness and macular volume are the most reported indicators to measure retinal atrophy on OCT. It has been shown that pwMS with a pRNFL thickness of less than or equal to 87 μm (88 μm) measured with Spectralis (Cirrus) OCT devices had double the risk of disability worsening in the follow-up (68).

which led us to consider this measure as a component of the inclusion criteria. With respect to progression of structural abnormalities of the retina, an absolute thinning of pRNFL of more than 1.25 μm at 24 months against baseline is considered clinically meaningful. This threshold has been established previously as the upper limit to define stability in multiple sclerosis (69).

#### Visit schedule

2.3.5.

See Table 1.

### Pre-processing of data

2.4.

All study data will undergo plausibility checks including description of missings prior to further analysis. Definitions of progression events by EDSS or alternative definitions for secondary outcomes are applied as provided in section 2.3.

Data from technical recordings (Amsa, Motognosis Labs, MRI, and OCT) are continuously monitored by trained users to check usability and plausibility according to standard operating procedures for quality control (QC). Specifically, for Amsa and PASS-MS, presentations of all assessments are systematically inspected and evaluated for quality concerns following the QC pipeline developed by Röhling et al. (70).

For RGB-D camera based motion capture, both Amsa and PASS-MS, a list of task-specific kinematic parameters is generated according to custom scripts by the provider. Kinematic parameters include for example gait speed for the short walking tasks. Primary analysis will consider only one parameter per test condition, i.e., seven parameters.

### Data management

2.5.

Data flow is shown in Figure 1. Study data are stored in an study-specific Electronic Data Capture platform (REDCap) (71). The platform also enables remote data entry of PRO by patients themselves via personalized links. The study team provides the links to each participant at the appropriate timepoints throughout the observation period.

**Figure 1 fig1:**
[figure not shown]
Data flow.

For the technical assessments performed in this study (Amsa, PASS-MS/Motognosis Labs, MRI, OCT), test results (e.g., gait speed from PASS-MS, number of T2 lesions on MRI, pRNFL thickness in OCT) are only transferred into REDCap system after pre-processing as described in section 2.4 along with results of QC.

All pseudonymized raw data are digitally stored in separate archives on local platforms.

With regard to data imports from home-based repeated Amsa assessments, raw data and metadata are saved on and retrieved with the device after each 1-week assessment period by the provider. The provider, after checking for technical issues and completeness, transfers results of daily self-ratings and pseudonymized metadata and raw data from Amsa recordings to the study site. Data are provided for QC application as well as kinematic parameters for analysis and archiving.

Data from routine care are collected from treating neurologists using structured paper templates.

### Status of the study

2.6.

Approval of the institutional review board (Charité—Universitätsmedizin Berlin) was obtained on 21 October 2021 (EA1/293/21). The study is active with first patient first visit in June 2022.

### Statistical analysis plan

2.7.

Based on the study question, the primary hypothesis is to assess the accuracy of detecting disease progression by the repeated short motor assessments at 24 months, compared to progression defined by EDSS at 24 months and confirmed at 27 months.

The sample size is justified via the expected precision of the estimate of the area under the receiver operating characteristic curve (AUC) provided in terms of the 95% confidence interval. We hypothesize that the parameters derived from repeated short motor assessment at home can reliably identify disease progression compared to detection of progression according to EDSS.

If the AUC is 0.9, and the sample size is 150, from which 10% are diagnosed with a progression according to EDSS at 24 months, then the width of the 95% confidence interval will be 0.103. In case of a lower AUC, e.g., 0.8, the 95% confidence interval would be of width 0.138. These calculations were performed using nQuery version 8.7.0.0, procedure AOC6-1. Given these calculations, the expected precision of the estimated quantity seems sufficient to evaluate the exploratory research hypothesis of this study.

Given the baseline definition, the primary endpoint is analyzed as AUC of detection of disease progression according to the repeated short motor assessment at home compared to detection of disease progression according to the EDSS score at 24 months, confirmed at 27 months. The AUC is calculated alongside with the 95% confidence interval. Event of progression at 24 months detected by parameters from repeated short motor assessment at home is defined as observed reliable change in pre-defined direction of worsening in one or more of the parameters derived from this assessment. Threshold for reliable change will be defined based on analysis of baseline data. Secondary endpoint analyses are planned for MSWS-12, HAQUAMS, PGIC, CGI, MSFC, and 6 MW. Respective receiver operating characteristic curves and their AUC will be calculated based on published evidence on minimally important difference for MSFC, 6 MW, MSWS-12, and HAQUAMS while any transition in the direction of worsening will be considered an important change on PGIC and CGI.

Subgroup analysis are planned for stratification by age > 55 years vs. younger and EDSS < 3.5 vs. higher. Further exploratory subgroup analysis may be conducted for all endpoints, if there exist relevant subgroups, using standard statistical methods such as parametric or non-parametric location tests and regression methods.

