We aimed to address potential drawbacks of remote task-based assessment in study design and analysis plan. First, variability in task performance can be expected to be higher in unsupervised settings. We aim to mitigate this point by control of device set-up by a trained operator, standardized instructions and by technical design. Second, we apply a standardized quality control pipeline on recordings to identify relevant protocol deviations. Roehling et al. showed the feasibility but also the necessity for a *post hoc* quality control using this method of instrumented motion analysis (70). In this study, we extend this QC pipeline exploring its practicality to Amsa measurements. Furthermore, participants’ adherence is surely a concern in this long-term observation. A recent 8-week RCT study investigated participants’ short term adherence in using digital tools in multiple sclerosis. The average overall adherence for all three measurement tools (1. MS patient-reported outcome tool accessible via a smartphone app, 2. Floodlight open, a app-based assessment of hand and gait function, and 3. Fitbit, a smart watch for passive monitoring of sleep duration and quality) was 81% in the intervention group (90). Midaglia et al. analyzed the practicability of remote active testing and passive monitoring using digital tools in pwMS and showed 70% (16.68/24 weeks) adherence to active testing and 79% (18.89/24 weeks) to passive monitoring (74). Rates of attrition in application of remote assessment have not yet been reported over longer time-frames. In order to sustain adherence in our 24 months-study, participants will receive a reminder link about 4 weeks before the upcoming measurement and the Amsa device will be delivered by the study team at the appropriate time.

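### The two stated 95% CI widths for the AUC (0.103 and 0.138) are half-widths; under the formula that reproduces them the full intervals are about 0.21 and 0.28 wide

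*Protocol article*

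**What the plan says.** The protocol article, section 2.7 (Statistical analysis plan), bases the sample size on the expected 95% confidence interval for the AUC of the home-based motor assessment against EDSS-defined progression. The inputs are "If the AUC is 0.9, and the sample size is 150" and "from which 10% are diagnosed with a progression according to EDSS at 24 months". The result for AUC 0.9 is "then the width of the 95% confidence interval will be 0.103". For an AUC of 0.8, "the 95% confidence interval would be of width 0.138". The calculations are attributed to nQuery 8.7.0.0, procedure AOC6-1, without the variance formula. The section then concludes that "the expected precision of the estimated quantity seems sufficient to evaluate the exploratory research hypothesis of this study". It gives no other basis for the number 150.

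**The concern.** Ten percent of 150 is 15 progressors. An interval only 0.10 to 0.14 wide looks too narrow for an AUC estimated from 15 events. Read literally, the printed widths place the limits at about 0.85 to 0.95 for an AUC of 0.9 (0.9 ± 0.103/2) and about 0.73 to 0.87 for an AUC of 0.8 (0.8 ± 0.138/2). If the figures are really half-widths, a reader is shown about half the true uncertainty, and the statement that the precision suffices rests on the wrong numbers.

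**Working it through.** **Inputs (section 2.7).** N = 150; 10% progressors, so n1 = 15 and n0 = 135; AUC A = 0.9 or 0.8; 95% confidence, taken as two-sided (z = 1.96).

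**Formula.** The article does not give the one used. The Hanley-McNeil variance is tried first:

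SE² = [A(1−A) + (n1−1)(B1−A²) + (n0−1)(B2−A²)] / (n1·n0), with B1 = A/(2−A) and B2 = 2A²/(1+A). The interval is A ± 1.96·SE.

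**AUC 0.8.**
- B1 = 0.6667, B2 = 0.7111, A² = 0.64.
- Numerator: 0.16 + 14 × 0.02667 + 134 × 0.07111 = 0.160 + 0.373 + 9.529 = 10.062.
- SE² = 10.062/2025 = 0.004969; SE = 0.0705.
- 1.96·SE = 0.138. Interval 0.662 to 0.938; full width 0.276.
- Half of 0.276 is 0.138, the figure the article calls the width.

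**AUC 0.9.**
- B1 = 0.8182, B2 = 0.8526, A² = 0.81.
- Numerator: 0.09 + 14 × 0.00818 + 134 × 0.04263 = 0.090 + 0.115 + 5.713 = 5.917 (from unrounded terms).
- SE² = 5.917/2025 = 0.002922; SE = 0.0541.
- 1.96·SE = 0.106. Interval 0.794 to 1.006; full width 0.212.
- An AUC cannot exceed 1. With the upper limit capped, the interval is 0.794 to 1.000 and the full width 0.206.
- Half of 0.206 is 0.103, again the printed figure. It is half of a capped, asymmetric interval and not the distance to either limit, since those distances are 0.106 below and 0.100 above.

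**Can both figures be full widths?** Other calculations, at 15 versus 135 unless noted:

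| Method | Full width, AUC 0.9 | Full width, AUC 0.8 |
|---|---|---|
| Stated in the article | 0.103 | 0.138 |
| Hanley-McNeil (capped at 1) | 0.206 | 0.276 |
| Binormal (Obuchowski) variance | 0.225 | 0.284 |
| Logit-transformed interval | 0.232 | 0.277 |
| Simulation, equal-variance binormal | 0.160 | 0.232 |
| Single cutoff, sensitivity = specificity = AUC (assumed) | 0.160 | 0.213 |
| Hanley-McNeil, groups swapped (135/15) | 0.116 | 0.189 |
| Hanley-McNeil, balanced 75/75 | 0.103 | 0.142 |

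None gives both printed figures. The balanced split matches at 0.9 but misses at 0.8, and it contradicts the stated 10%.

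**Scale.** Under Hanley-McNeil with 10% progressors, uncapped full widths of 0.103 and 0.138 would take about 632 and 599 participants.

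**The case against.** - **The formula is inferred.** The article names the software procedure but not the variance formula, so the twofold factor belongs to the formula that reproduces the figures. Simulation gives smaller ratios: 0.160/0.103 = 1.55 and 0.232/0.138 = 1.68. This stands and is why the size is stated conditionally. It does not rescue the printed widths, because two matches to three decimals from the article's own inputs are unlikely to be chance.

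- **Some calculation could give a width that small.** The home-based event is defined as yes or no, so a single-cutoff AUC, (sensitivity + specificity)/2, is relevant. With a lopsided assumed split its Wald interval narrows: 0.97/0.83 gives about 0.107 at AUC 0.9, and 0.95/0.65 gives about 0.137 at AUC 0.8. So it cannot be said that no method yields such widths. But these splits are chosen to fit, differ between the two cases and miss both printed values.

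- **No criterion is missed.** The article sets no target width, null AUC or power, calls the hypothesis exploratory, and acknowledges in its Discussion the risk of too few progression events. This also stands. A reader might infer that 150 is too few or that the study cannot answer its question. The documents do not support that: at AUC 0.8 the lower limit of 0.66 still excludes 0.5, and whether 0.21 to 0.28 is precise enough is a judgement for the authors.

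- **Attrition.** A reader might go further and cut the sample to 70–80% evaluable, since the Discussion says participants' "adherence is surely a concern in this long-term observation" and cites 70% and 81%. Those are rates of adherence to digital tools in shorter studies, not proportions of people with an evaluable endpoint. Missed sessions within a week of up to 14 recordings do not by themselves lose a participant. The article supports no specific number of evaluable participants.

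**Conclusion.** The point holds as a misreported figure. The values 0.103 and 0.138 are half of the full interval widths (at AUC 0.9, half of the interval capped at 1). The full widths are about 0.21 and 0.28, so precision is overstated about twofold under Hanley-McNeil. This assumes 15 versus 135, a two-sided 95% level and all 150 participants evaluable. Because these two figures are the only stated support for the sample size, and the sufficiency sentence is drawn directly from them, they should be corrected. It does not follow that the sample size must change. Nor is the method for the final interval at fault, since section 2.7 says only "The AUC is calculated alongside with the 95% confidence interval" and the choice can be left to the analysis plan.

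**What to change.** In section 2.7, either relabel 0.103 and 0.138 as half-widths, noting that the first is half of an interval capped at 1, or replace them with: the 95% confidence interval would run from about 0.79 to 1.00 (width 0.21) at an AUC of 0.9 and from about 0.66 to 0.94 (width 0.28) at an AUC of 0.8, if all 150 participants are evaluable. Naming the variance formula behind the software procedure would settle the inference made here. Then reassess the sufficiency sentence against the corrected widths and either keep it with a reason or soften it. This is a wording change: sample size, visits and conduct are untouched. The only cost is that the stated precision looks less favourable.

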At a time when chronic disease processes represent the target for future interventions in MS, improving the operational definitions of disability progression remains a key priority of MS research (20). Technical measures to quantify specific functions have been explored in this respect. Walking impairments are reported in up to 75% by people with MS (pwMS) (21) and thus pose a good candidate for quantitative assessment in this disorder. Consequently, the instrumental assessment of gait, mobility or other specific functions has received attention in MS research (15, 22–26). Interestingly, instrumental gait analysis has shown dysfunctional walking patterns despite clinically normal gait function even in early stage disease (27). Technical methods of remote assessment such as commercial activity trackers have a part in recent MS trials protocols (28). However, sources of variance and appropriate definitions of relevant change still need to be established for emerging digital biomarkers (29, 30).

Following this strategy, this investigation aims to devise and evaluate an instrumental definition of CDP in early RRMS by episodic patient self-assessment of motor symptoms at home. Among the various technologies available, we chose a visual-perceptive technology based on commercial RGB-D cameras. As a marker-free method this study applies a consumer-grade RGB-Depth (RGB-D) camera (Microsoft Azure Kinect®) combined with customized software (Motognosis Amsa) for motion capture at home as the primary outcome. As a marker-free method, it has high potential for clinical utility and RGB-D technology has been explored for the purpose of task-based motor assessment in various neurological conditions in research settings (31–34). As a novelty, we here turn the patient into the central operator and home-based application into the primary outcome. This enables data acquisition at higher frequency compared to conventional protocols that rely on in-patient research visits.

Primary endpoint is the accuracy of detection of progression events at 24 month compared to progression events defined as 3-month CDP in EDSS. Relation of such definitions to patients’ reports of function and impairment as well as structural change on MR imaging and optical coherence tomography (OCT) will complement the final analysis.

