### Study design

2.1.

The study is a single-center prospective observational cohort study. Study data combines observations from different sources: patients’ remote self-assessment, data from treating neurologists obtained in routine clinical care—both performed semiannually—and data from annual in-person study visits at an academic clinical research center. The primary outcome consists of home-based recordings of short motor tests (Amsa, Motognosis GmbH, Berlin, Germany) performed twice a day for a period of 1 week every 6 months. Patient-reported outcomes is acquired every 6 months using validated questionnaires on specific functions, impairments and quality of life.

Data requested from treating neurologists comprise the Multiple Sclerosis Functional Composite (MSFC-3) (35), the global assessment of the change since last observation [clinical global impression of change (CGI) (36)] and information on relapse events/relapse therapy including recovery, change of therapy or comorbidity since prior visit.

Annual study visits at the research site comprise clinical and functional assessment including Motognosis Labs as well as imaging of brain (MRI) and retina (OCT) detailed below.

The observation period is 24 months for the primary endpoint with an additional clinical assessment at 27 months to confirm progression defined by EDSS.

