### Data acquisition

2.3.

An overview of the visit schedule is provided in Table 1.

**Table 1 tab1:** Overview study assessments and visit schedule.

Assessment	Rater	Screening	Baseline visit (V) 1	Visit 2	Visit 3	Visit 4	Visit 5	Visit 6
			Month 1	Month 6	Month 12	Month 18	Month 24	Month 27
Written informed consent	Investigator	□						
Assessment of in- and exclusion criteria/confirmation of in and exclusion criteria	Investigator	□	□		□		□	□
Assessment/Follow up of patients’ characteristics (diagnosis ascertainment, comorbidities, age, height, weight, relapses in past 24 months/since last visit, current symptoms, treatment: current treatment at baseline, change of treatment at follow-up)	Investigator		□		□		□	□
EDSS	Investigator	□	□		□		□	□
MSFC-4	Study assistant		□		□		□	□
6-min walk test	Study assistant		□		□		□	□
PASS-MS assessment of motor functions			□		□		□	□
PRO PGIC	Patient		□	●	□	●	□	□
PRO MSWS-12	Patient		□	●	□	●	□	□
PRO FSMC	Patient		□	●	□	●	□	□
PRO NRS	Patient		□	●	□	●	□	□
PRO HAQUAMS	Patient		□	●	□	●	□	□
PRO PHQ-9	Patient		□	●	□	●	□	□
PRO GLTEQ	Patient		□	●	□	●	□	□
PRO EQ-5D-5L	Patient		□	●	□	●	□	□
PRO BPI	Patient		□	●	□	●	□	□
Instruction (Reinstruction if needed) of use for Amsa	Study assistant		□	(●)	(□)	(●)	(□)	
Amsa assessment recorded twice a day over 7 days	Patient		●	●	●	●	●	
Reporting of AE and safety issues related to Amsa self-assessment	Patient		●	●	●	●	●	
PRO Pain-NAS, EQ-VAS, state fatigue once a day on each day of functional assessment	Patient		●	●	●	●	●	
Usability rating	Patient		●	●	●	●	●	
Brain MRI			□				□	
OCT			□				□	
Clinical global impression of change	Treating neurologist			◊	◊	◊	◊	◊
Most recent relapse incl treatment and course of remission	Treating neurologist		◊	◊	◊	◊	◊	◊
Current medication/Change in medication from baseline/comorbidities	Treating neurologist		◊	◊	◊	◊	◊	◊
MSFC-3	Treating neurologist		◊	◊	◊	◊	◊	◊

The components of each visit are denoted as (□) annual research grade assessment at study center, (●) remote self-assessment of motor functions at home (Amsa) and (◊) clinical data collected from routine visits.

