## Glossary

AUC: Area under the receiver operating characteristic curve
BVL: Brain volume loss
BPI: Brief pain inventory
CDP: Confirmed disability progression
CGI: Clinical global impression of change
DMTs: Disease modifying therapies
EDSS: Expanded disability status scale
FSMC: Fatigue scale for motor and cognitive functions
GLTEQ: Godin leisure-time exercise questionnaire
HAQUAMS: Hamburg quality of life questionnaire for multiple sclerosis
MRI: Magnetic resonance imaging
MS: Multiple sclerosis
MSFC: Multiple sclerosis functional composite
MSWS-12: The multiple sclerosis walking scale-12
NAS: Numerical analog scale
NEDA: No evidence of disease activity
NRS: Numeric rating scale
OCT: Optical coherence tomography
PASAT: Paced auditory serial addition test
PGIC: Patients’ global impression of change
PHQ-9: Patient health questionnaire-9
pRNFL: Peripapillary retinal nerve fiber layer
PRO: Patient reported outcome
pwMS: People with multiple sclerosis
QC: Quality control
RCTs: Randomized controlled trials
REDCap: Research electronic data capture
RGB-D: RGB-D camera that provides both depth (D) and color (RGB) data
RRMS: Relapsing–remitting multiple sclerosis
SDMT: Symbol digit modalities test
SUS-Plus: System usability scale plus
V: Visit
VAS: Visual analog scale
VPC: Visual perceptive computing
3 m-CDP: 3-month confirmed disease progression
6 MW: 6-min walk

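### The Amsa event is unconfirmed worsening in a single week at month 24, so the primary comparison alone does not evaluate the instrumental definition of confirmed progression that the Introduction sets as the aim

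*Protocol article*

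**What the plan says.** - **Aim.** The Introduction says that the investigation "aims to devise and evaluate an instrumental definition of CDP in early RRMS by episodic patient self-assessment of motor symptoms at home". The Glossary entry reads "CDP: Confirmed disability progression".
- **Amsa event.** Section 2.7 states: "Event of progression at 24 months detected by parameters from repeated short motor assessment at home is defined as observed reliable change", continuing "in pre-defined direction of worsening in one or more of the parameters derived from this assessment". The reliable-change threshold is to come from baseline data. Section 2.4 adds: "Primary analysis will consider only one parameter per test condition, i.e., seven parameters".
- **Amsa schedule.** In Table 1 the row "Amsa assessment recorded twice a day over 7 days" is marked at baseline and at months 6, 12, 18 and 24. The month-27 cell is empty.
- **EDSS comparator.** Section 2.1 provides for an "additional clinical assessment at 27 months to confirm progression defined by EDSS". Section 2.3.4.2 requires the EDSS increase to be present at month 24 and confirmed at month 27.
- **Related provisions.** The Discussion promises to take day-to-day variability within each Amsa week into account when defining change. Section 2.3.1 records pain, health status and fatigue on each Amsa day. The Abstract mentions secondary analyses of the time course of motor parameters. PASS-MS is scheduled at baseline and at months 12, 24 and 27.

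**The concern.** One side of the primary comparison must be sustained over three months; the other need only be present in one week. The article's own reasoning makes this matter. The Introduction treats the length of the confirmation period as the main determinant of a robust progression definition and lists short-term fluctuation as an important source of variability. The Discussion says the target is chronic progression independent of relapse.

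Up to 14 recordings in a week average out single-day noise. They do not average out a week that is poor throughout, for example because of an intercurrent illness or a relapse. Such a patient becomes an Amsa progressor, and no later Amsa week can show whether the change lasted.

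What is at stake is interpretation. If specificity is low, readers will not know whether Amsa picked up passing worsening or lasting change that the EDSS missed. If it is high, the study will still have evaluated an unconfirmed event under the name of a confirmed one.

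**Working it through.** The plan gives no figure for this point: no threshold, no reliability and no correlation between parameters. The first step therefore compares the text, and the rest is illustration under stated assumptions.

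1. **Text.** Aim: confirmed progression. Index event: change at month 24, no second time point. Later Amsa confirmation: impossible, because no week follows month 24. Earlier support from month 18: possible on the schedule, but no section requires it. Comparator: months 24 and 27. The daily ratings and the day-to-day variability provision concern fluctuation inside a week and add no persistence rule.

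2. **Assumptions for the illustration.** Stable patients; seven parameters (section 2.4); equal, independent week-level error with variance s² at baseline, month 18 and month 24; one-sided limits of 1.645 or 1.96 SD of the change; correlation between parameters of 0 or 0.5. Each change has variance 2s². Two changes from the same baseline have covariance s², so their correlation is s²/2s² = 0.5.

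3. **Chance worsening, single week versus the same parameter in both weeks (simulation).**

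| Case | Limit 1.645 | Limit 1.96 |
|---|---|---|
| One parameter | 5.0% → 1.2% | 2.5% → 0.5% |
| Any of seven, correlation 0.5 | 20.3% → 6.4% | 11.6% → 2.6% |
| Any of seven, correlation 0 | 30.2% → 8.2% | 16.2% → 3.2% |

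4. **In patients.** Section 2.7 assumes 150 participants with 10% progressing: 15 progressors and 135 non-progressors. At correlation 0.5, 135 × 0.203 ≈ 27 chance positives fall to 135 × 0.064 ≈ 9. At the stricter limit, 135 × 0.116 ≈ 16 fall to 135 × 0.026 ≈ 4.

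5. **Cost in sensitivity.** If onset is uniform over 24 months, (24 − 18)/24 = 25% of events start after month 18 and cannot meet the rule. With an assumed sensitivity of 0.8, the sustained rule has at most about 0.8 × 0.75 = 0.60. Among 15 progressors, that is 12 detected falling to 9.

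6. **Net effect on AUC.** For a yes/no index event, AUC = (sensitivity + specificity)/2. At correlation 0.5:
   - Limit 1.645: single week (0.8 + 0.797)/2 = 0.80. Sustained: (0.6 + 0.936)/2 = 0.77, or (0.8 + 0.936)/2 = 0.87 if no sensitivity were lost.
   - Limit 1.96: single week (0.8 + 0.884)/2 = 0.84. Sustained: (0.6 + 0.974)/2 = 0.79, or (0.8 + 0.974)/2 = 0.89 if no sensitivity were lost.
   - Break-even with 25% late onset: the specificity gain equals the sensitivity loss at 0.139/0.25 ≈ 0.56 (limit 1.645) or 0.090/0.25 = 0.36 (limit 1.96). Above these sensitivities the sustained rule has the lower AUC.

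**The case against.** The strongest reply is that the asymmetry is the research question. Testing an earlier and cheaper index measure against a later and stricter reference is ordinary in accuracy studies, and the Discussion hopes that a new definition will shorten observation. A false positive from a bad week is then genuine test error and belongs in the specificity. This stands, and it is why the primary should not change.

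A second reply is that the phrase about an instrumental definition of CDP occurs once, in the Introduction, while the Abstract speaks more loosely of a novel definition of disease progression. This makes the labelling part of the point a wording matter. It does not supply a persistence rule.

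A reader might also draw stronger conclusions that the documents do not support:

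- **That the primary is invalid, or its AUC lowered for reasons unrelated to the technology.** Susceptibility to a poor week is a property of a one-week test.
- **That confirmation would raise the AUC.** The working shows that it can fall.
- **That a patient who has recovered in motor terms by month 27 can never be an EDSS progressor.** The EDSS also rests on functional system scores, so it can rise without the Amsa tasks worsening.
- **That the intermediate Amsa weeks will go unused.** The Abstract announces time-course analyses, and details may sit in a plan not shown here.
- **That PASS-MS at month 27 can simply serve as the confirmation.** Section 2.3.4.5 describes a different camera and an operator-guided setting, and the Introduction warns that clinic and home performance may differ.

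**Conclusion.** The point holds as a gap between the stated aim and the event that is analysed. The Amsa event is unconfirmed, the EDSS event is confirmed, and the article specifies nothing that distinguishes a transiently poor month-24 week from sustained change. The primary comparison remains sound for the narrower question it answers.

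The size cannot be read from the documents. The fall in chance positives (about 20% to 6%, or 12% to 3%, at correlation 0.5) rests on assumed error and correlation, applies only to the month-18-plus-24 rule, and takes the reliable-change limit to hold its nominal rate. The last assumption may be generous, because the threshold comes from baseline data and Table 1 has only one baseline Amsa week, which cannot show week-to-week variation over months. The direction of the AUC change is open. This is an inexpensive improvement to an exploratory study, not a flaw that undermines it.

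**What to change.** 1. Keep the primary analysis as it is.
2. Describe its Amsa event as unconfirmed instrumental worsening at month 24, and do not call that event an instrumental definition of CDP.
3. Pre-specify one secondary analysis of sustained instrumental worsening: the same Amsa parameter beyond the reliable-change threshold at both months 18 and 24. Report sensitivity, specificity and AUC against 3 m-CDP next to the primary, so that the trade-off is visible.
4. If month-27 PASS-MS is used, treat it as supporting evidence only, with its own reliable-change threshold taken from PASS-MS data.
5. State the limitation that the sustained rule misses onset after month 18.

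The cost is wording and one additional analysis, fixed before the follow-up data are examined. All the data are already scheduled, so no visit or device week is added. With about 15 expected progressors, each patient moves sensitivity by 1/15 ≈ 6.7 percentage points, so the comparison of the two rules will be descriptive.
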